### Intervention training

All CHTC interventionists and supervisors – regardless of site – complete a training sequence that includes CHTC and MI components. MI training involves attendance at a 2-day workshop that covers basic MI concepts, processes, and skills as well as strategies, processes and techniques unique to the delivery of MI with couples. CHTC training follows [name] and [name]’s curriculum, as adopted by CDC. Afterwards, providers complete a series of mock sessions. These begin with individual MI mocks to consolidate basic counseling skills. Subsequently a sequence of 4 CHTC mocks is completed so providers can practice each formulation of HIV test result delivery (concordant negative, concordant positive, and serodiscordant). The last 3 CHTC mocks include the SUM component.

### Fidelity monitoring and supervision

Drs. [name] or [name] provide feedback on all mocks based upon review of audio recordings. In addition, mock sessions are recorded and fidelity assessed using the CDC’s CHTC fidelity checklist [33]. Fidelity to MI during SUM completion is evaluated using a modified version of the Motivational Interviewing Treatment Integrity system Moyers et al. [11] augmented with codes developed by [name] et al. [21] specifically to assess the fidelity of MI delivered to couples.

### Primary outcomes

#### Illicit drug use

Will be operationalized as the odds of drug use in the past 30 days indicated by self-report on the Time-line Follow-back (TLFB) interview. Biologically, the occurrence of drug use will be assessed via urine assay.

#### HIV transmission risk behavior (TRB)

Primary Analyses focus on three dichotomous behavioral indicators of TRB These include: (1) Condomless anal sex (CAS) with a casual partner in the absence of PrEP; (2) CAS with a sero-discordant main partner (whose viral load is detectible) or concurrent CAS between main and casual partners in the absence of PrEP; (3) Any chlamydia or gonorrhea diagnosis in the absence of PrEP.

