Initial pilot results [20] indicated that completion of the SUM alone was associated with statistically significant decreases in the odds of drug use (*B* = − 3.62; *p* = .03) and drug use related problems as measured by the Drug Abuse Screening Test (DAST-10) [17] (*B* = − 0.75; *p* = .02) at 1-month post-intervention. While CT videos were not independently associated with reductions in drug use or DAST-10 scores; they significantly enhanced the long-term benefits of SUM completion. At 3-month and 6-month follow-up the SUM was only associated with significant decreases in the odds of drug use (*B* = − 2.79; *p* = .013 and *B* = − 3.93; *p* = .014 respectively) and DAST-10 scores (*B* = − 0.64; *p* = .01 and *B* = − 0.79; *p* = .003 respectively) among men who viewed the CT videos. In a direct comparison between the CHTC as usual condition and those participants who received both *We Test* adjunct components (CHTC+SUM+CT video), the combined condition had significantly lower odds of drug use at 1- and 3-month follow up and significantly lower DAST-10 scores at all follow-up time-points.

While promising, the results of [name] et al. [20] were limited in several ways. First, their study did not include biological markers for drug use and sexual risk taking to validate self-report responses. Second, the most distal follow-up was 6-months post-intervention. This was not sufficiently long enough to observe decay in the treatment effect for substance use outcomes. This limited the development of guidance or recommendations on the timing of CHTC-retesting with *We Test* module delivery. The next step in this program of research is to conduct a full scale efficacy trial that incorporates the use of biological markers in addition to self-reported behavioral data and a more extensive follow-up period with an expanded potential to observe decay in the intervention effect.

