### Eligibility criteria

Participants must fulfill the following inclusion criteria to be enrolled in the study. In each couple, both partners must indicate cismale gender and be 17 years of age or older. In addition, at least one participant in each couple must (1) be aged 17 to 29 years; (2) self-report an HIV-negative or unknown sero-status; (3) report use of at least 1 illicit drug (cocaine/crack, opiates, misuse of prescription medication, stimulants, psychedelics, ecstasy, ketamine, GHB) in the past 30 days, (4) have engaged in CAS with a casual partner or a main partner who is non-monogamous or sero-discordant in the past 90 days, (5) live in the New York City or Detroit metropolitan area, and (6) be able to speak and read in English.

Participants will be excluded from the study if they indicate signs of acute suicidality; gross impairment in cognitive functioning; or any history of intimate partner violence and current safety concerns in the current relationship. The trial does not place restrictions on concomitant receipt of care for substance use or HIV prevention.

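### The TRB indicators score HIV-positive participants inconsistently: viral suppression counts in only one limb, and PrEP is the sole exemption elsewhere

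*Protocol article*

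**What the plan says.** The section on HIV transmission risk behavior, under Primary outcomes, states: "Primary Analyses focus on three dichotomous behavioral indicators of TRB". The components are:

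- Indicator 1: "Condomless anal sex (CAS) with a casual partner in the absence of PrEP".
- Indicator 2, main-partner limb: "CAS with a sero-discordant main partner (whose viral load is detectible").
- Indicator 2, concurrency limb: "concurrent CAS between main and casual partners in the absence of PrEP".
- Indicator 3: "Any chlamydia or gonorrhea diagnosis in the absence of PrEP".

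Under Eligibility criteria the serostatus requirement is introduced by "at least one participant in each couple must" and reads "self-report an HIV-negative or unknown sero-status". The other partner may therefore be HIV-positive, and a sero-discordant main partner is among the qualifying exposures. Primary analyses of intervention effects keeps every randomized participant in the model, nested in couples. Under Moderation/mediation analyses, couples' HIV status is examined as a moderator, with viral suppression and PrEP uptake considered.

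On the pilot, Background notes that "their study did not include biological markers for drug use and sexual risk taking to validate self-report responses".

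**The concern.** The definition uses two kinds of protection, PrEP and viral suppression, but not consistently. It accepts in one limb that a man with an undetectable viral load poses no counted risk, then ignores his suppression in the other three components. Those components can be cleared only by PrEP, which an HIV-positive participant would not be using.

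Three consequences follow:

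- Some men are counted as TRB although the protocol's own logic would count them as protected.
- Partners in a discordant couple can receive different scores for the same act, in a model that nests partners within couples.
- The one biological TRB indicator depends on PrEP status, so it is a restricted check on self-reported CAS, and it can move when PrEP use changes while sexual behavior does not. This bears on Objectives, where a TRB reduction is hypothesized to come through less drug use.

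**Working it through.** **Plan's own figure.** The documents give no HIV-positive share, suppression rate, PrEP rate or TRB base rate. The only figure tied to this outcome is the power statement under Sample size, and this point does not rest on it.

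**Step 1: apply the rules as written.** Assume PrEP means the participant's own and the behavior or diagnosis in each column is present. The main-partner column concerns discordant couples.

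| Participant | Casual CAS (1) | Main-partner CAS (2) | Concurrent CAS (2) | Chlamydia/gonorrhea (3) |
|---|---|---|---|---|
| HIV-negative, on PrEP | 0 | turns on partner's viral load, and on PrEP if the closing PrEP phrase covers both limbs | 0 | 0 |
| HIV-negative, no PrEP | 1 | 1 if partner detectable, otherwise 0 | 1 | 1 |
| HIV-positive, suppressed | 1 | 0 | 1 | 1 |
| HIV-positive, detectable | 1 | 0, as his partner has no viral load | 1 | 1 |

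The suppressed man scores the same as the detectable man in every column. In the main-partner column, an HIV-negative man without PrEP scores 1 while his detectable partner scores 0 for the same act.

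**Step 2: inflation of the level (indicator 1).** Let c be the casual-CAS rate, taken as equal in all groups, h the HIV-positive share, q PrEP use among the others, and s the share of HIV-positive men who are suppressed. All are assumptions.

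- Prevalence as written: c × [h + (1 − h)(1 − q)].
- Part due to suppressed men: c × h × s.
- Their share of positives: h × s / [h + (1 − h)(1 − q)]; c cancels.

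With q = 0.30:

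- h = 0.05, s = 0.60: 0.03 / 0.715 = 4%.
- h = 0.10, s = 0.80: 0.08 / 0.73 = 11%.
- h = 0.20, s = 0.95: 0.19 / 0.76 = 25%.

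If h and s are equal across arms, as randomization gives in expectation, this adds no arm difference.

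**Step 3: dilution.** Assume true TRB of 20% vs 12% in the other men: OR = (0.12/0.88) / (0.20/0.80) = 0.55. Let a fraction f of participants be suppressed men, with casual CAS of 50% in the control arm.

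- No effect in these men (50% in both arms). At f = 0.20: 0.80 × 0.20 + 0.20 × 0.50 = 26.0% vs 0.80 × 0.12 + 0.20 × 0.50 = 19.6%, OR 0.69. At f = 0.05 the OR is 0.59.
- Same OR in these men (50% vs 35.3%). At f = 0.20: 26.0% vs 16.7%, OR 0.57. At f = 0.05 the OR is 0.55.

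Dilution thus runs from almost none to an OR of 0.69, depending on an effect in HIV-positive men that the documents do not give.

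**Step 4: PrEP alone.** Take h = 0 and hold behavior fixed. PrEP use of 40% rather than 30% multiplies an indicator restricted to men without PrEP by 0.60/0.70 = 0.86. With c = 0.40, indicator 1 goes from 28% to 24% (OR 0.81). The same factor applies to indicator 3 if STI risk is taken as unrelated to PrEP use. The documents do not predict such an arm difference; this shows only how sensitive the scoring is.

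**The case against.** **Netting out PrEP is defensible.** The outcome is HIV transmission risk, and PrEP lowers it. PrEP is discussed in CHTC in every arm, so an arm difference in uptake is possible but not predicted. Attribution to drug use is tested through mediation models. This stands: the PrEP-restricted indicators may remain.

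**The text is condensed.** It does not say whose PrEP counts, and the viral-load parenthesis could be meant at couple level, in which case both partners score alike. Detailed scoring may sit in a document not shown. This limits the claim to the literal reading. It does not explain why suppression enters one limb only, and the moderation analysis does not change how anyone is scored.

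**Two stronger readings are not supported.** A reader might infer that serostatus can produce a TRB difference between arms. Stable serostatus is balanced by randomization in expectation, so misscoring raises the level in every arm.

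A reader might also infer a large power loss, for example from about 0.66 to 0.39 with 240 vs 240 and 20% suppressed men. That figure assumes no intervention effect in HIV-positive men, which the documents do not say. With the same OR in these men, power is about 0.70. The benchmark is also wrong: with these men enrolled and scored 0, power is about 0.55, not 0.66. No power loss should be claimed.

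**Indicator 3 still has value.** It carries the same PrEP condition as indicator 1, and the chlamydia/gonorrhea tests are described without a PrEP restriction, so unrestricted results will exist. It is therefore a restricted check, not a useless one.

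**Conclusion.** The concern holds as an internal inconsistency in a primary outcome definition. On the natural reading that PrEP is the participant's own, virally suppressed HIV-positive men are scored as TRB for casual CAS, concurrent CAS and STIs, against the logic of the main-partner limb. Read literally, that limb can also split the score for one act between partners.

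The result is an inflated TRB level (4–25% of indicator 1 positives under the assumed shares) and possible dilution of unknown size. The scoring does not by itself create an arm difference. Indicator 3 gives only a PrEP-restricted check on self-reported CAS and could shift with PrEP use alone. The definition should be corrected before analysis, but the point does not undermine the trial's design.

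**What to change.** 1. State whose PrEP and whose viral load count. In all three indicators, treat a participant as protected if he is HIV-negative or of unknown status and on PrEP, or HIV-positive and virally suppressed.
2. Score main-partner CAS in a discordant couple once, at couple level and identically for both men, from the HIV-positive partner's viral load and the HIV-negative partner's PrEP.
3. Keep the PrEP-restricted STI indicator and add chlamydia/gonorrhea regardless of PrEP as a supporting biological outcome, from the tests already described under Data collection for primary outcomes.

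The rule should not require a casual partner's serostatus or PrEP use, since the timeline follow-back items listed there do not include them.

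The cost is re-coding, one extra analysis, and confirming that every HIV-positive participant's viral load is recorded. Indicator 2 already needs that value in discordant couples.

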### Participant timeline

Figure 1

**Fig. 1 Fig1:**
[figure not shown]
Participant Timeline

#### Sample size

Power analyses were generated by Monte Carlo simulation using Mplus (version 8.0). All estimates were based upon 10,000 sample replications and power was defined as the percentage of randomly generated samples in which the specified parameter was statistically significant. All simulated models were multi-level, nesting participants (at Level 1) within couples (at Level 2). Models focused on detecting between-condition differences at any one follow-up time-point (as opposed to predicting slope factors). This allowed for more direct extrapolation of error variances from existing baseline data and is consistent with the primary aim of the study. The main effects of the two interventions (the drug use calendar and video-based communication skills training) as well as their interaction were modeled at level 2. Based upon the results of our previous studies, we anticipate 80% minimum follow-up retention at 12 months. These analyses therefore reflect a conservative analytic sample of 240 couples (480 individuals).

Analyses indicated that the proposed study has power > .80 to detect a simple main effect of SUM and/or CT videos corresponding to a 15% reduction in the odds of drug use and a 1.0 point reduction in DAST scores at any follow-up time point. The proposed study has power > .80 to detect a 2% reduction in the odds of reporting HIV TRB. Effects of these magnitudes are plausible given our pilot data. *We Test* pilot data have indicated that mediational pathways linking CT videos with drug use outcomes likely involve depression. The effects of viewing ACTV were generally small across indices of communication skills and psychological functioning. The most promising (statistically significant) effects were associated with improvements in self- disclosure communication (β = .13) and depression (β = −.16). Notably, the indirect pathway between CT and depression through self-disclosure communication was of moderate size (β = −.12) indicating that communication skills may be one mechanism by which ACTV yields reductions in depression. Depression scores were, in turn, positively associated with the odds of drug use (β = −.45) and DAST scores (β = .06). Using these effects as preliminary estimates, Monte Carlo simulations suggested that the proposed study design has power > .80 to detect the significance of direct pathways and implied indirect effects of intervention.

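### The power above .80 stated for a 15% cut in the odds of drug use and a 2% cut in the odds of TRB cannot be right as written for 240 couples

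*Protocol article*

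**What the plan says.** The Sample size section reports two-level Mplus simulations (men within couples) of between-condition differences at a single follow-up, with both main effects and their interaction at couple level. Because "we anticipate 80% minimum follow-up retention at 12 months", the figures rest on a "conservative analytic sample of 240 couples (480 individuals"). On that basis power is said to exceed .80 for a "simple main effect of SUM and/or CT videos corresponding to a 15% reduction in the odds of drug use". The next sentence reads: "The proposed study has power > .80 to detect a 2% reduction in the odds of reporting HIV TRB". The section then adds: "Effects of these magnitudes are plausible given our pilot data".

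Both outcomes are binary at the level of the man. For drug use the Primary outcomes section says: "Will be operationalized as the odds of drug use in the past 30 days indicated by self-report". For TRB it says: "Primary Analyses focus on three dichotomous behavioral indicators of TRB". The article gives no alpha, allocation ratio, control rates or intra-couple correlation for the power calculation.

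**The concern.** A 15% reduction in odds is an odds ratio of 0.85, and a 2% reduction is 0.98. Both are very small effects for a binary outcome in 480 men. One fixed design is also said to reach the same power for two effects whose log odds ratios differ about eightfold (0.163 v 0.020).

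These two sentences are the only detectable effects the article gives for its two named primary outcomes. If they are wrong, a reader of a null result could believe that the trial was able to see reductions far smaller than it can.

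**Working it through.** **Inputs from the article:** 240 couples, 480 men; one follow-up; four conditions; odds ratios 0.85 and 0.98; stated power above .80.

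**Assumptions, because the article is silent:** two-sided alpha 0.05; equal allocation; control rate p1 from 2% to 98%; ICC from 0 to 1.

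**Contrast.** A factorial main effect over the margin compares 120 v 120 couples, so n = 240 men per level. If the simple main effect is the effect of one component with the other absent, it compares 60 v 60 couples, so n = 120.

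**Formula (Wald test of a log odds ratio, clusters of two).**
- p2 = OR·o1/(1 + OR·o1), with o1 = p1/(1 − p1)
- SE² = (1 + ICC)·[1/(n·p1(1 − p1)) + 1/(n·p2(1 − p2))]
- Power = Φ(|ln OR|/SE − 1.960) + Φ(−|ln OR|/SE − 1.960)

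**Attempt to reproduce the drug-use figure.** The most favourable case is n = 240, ICC 0, p1 = 0.52. Then o1 = 1.083, p2 = 0.479, SE² = 0.0167 + 0.0167 = 0.0334 and SE = 0.183. With |ln 0.85| = 0.1625 the ratio is 0.889, so power = 0.142 + 0.002 = **0.144**.

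**Attempt to reproduce the TRB figure.** At p1 = 0.50, SE = 0.183 and |ln 0.98| = 0.0202. The ratio is 0.111, so power = 0.032 + 0.019 = **0.051**, essentially the type I error rate.

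**Maximum power over all control rates:**

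| Contrast | ICC | OR 0.85 | OR 0.98 |
|---|---|---|---|
| 120 v 120 couples | 0 | 14.4% | 5.1% |
| 120 v 120 couples | 0.3 | 12.2% | 5.1% |
| 120 v 120 couples | 1 | 9.6% | 5.1% |
| 60 v 60 couples | 0 | 9.6% | 5.1% |
| 60 v 60 couples | 1 | 7.3% | 5.0% |

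A simulation of the 2×2 logit with interaction and cluster-robust errors, at control rates of 30% and 50%, agrees. For 0.85 it gives 8.6-15.5% (margin) and 6.2-10.3% (single cell); for 0.98 it gives 3.9-5.5%.

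**Variants on the odds scale for 0.85 (margin).** One-sided 0.05 gives 22.5% and one-sided 0.10 gives 34.7%. All 300 couples (240/0.80) without dropout give 16.9%. Significance at any of four independent follow-ups gives 46%, and 19% for OR 0.98. None reaches .80.

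**Couples needed.** Men per level equal total couples (two men per couple, two levels). At p1 = 0.50 and ICC 0, n = (1.960 + 0.842)²·[1/(p1(1 − p1)) + 1/(p2(1 − p2))]/(ln OR)². For 0.85 this is 7.85 × 8.03/0.0264, about 2,385 couples. For 0.98 it is about 153,850.

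**Odds ratio detectable with 80% power at control rates 30%, 50%, 70%:**

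| Contrast | ICC 0 | ICC 0.3 |
|---|---|---|
| 120 v 120 couples | 0.54, 0.59, 0.58 | 0.49, 0.55, 0.54 |
| 60 v 60 couples | 0.40, 0.47, 0.47 | 0.34, 0.42, 0.42 |

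**Reading 15% as percentage points** (power for two proportions, same control rates):

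| Contrast | ICC 0 | ICC 0.3 |
|---|---|---|
| 120 v 120 couples | 0.98, 0.92, 0.93 | 0.94, 0.83, 0.85 |
| 60 v 60 couples | 0.80, 0.65, 0.67 | 0.69, 0.54, 0.56 |

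**Reading 2% as percentage points of total TRB effect (margin, ICC 0).** Power is 0.20 at a control rate of 5% and 0.06-0.07 at 30-70%. In the extreme case of a fall from 2% to none it depends on the test: about 0.35 (Fisher exact), 0.56 (normal approximation, control rate just above 2%) or 0.71 (uncorrected chi-square). All are below .80.

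**The case against.** The strongest reply concerns TRB. The Objectives section says that no direct effect on TRB is expected and that the study was powered for indirect effects through drug use. Power for an indirect effect depends on its two paths, not on the total effect. As an illustration with assumed inputs, let drug use fall from 50% to 35% and let TRB be 13.3 points more common among users. The implied indirect reduction is 0.15 × 13.3 = 2.0 points. Simulated joint-significance power with 120 v 120 couples is then about 0.7 to 0.9 for TRB rates of 10-30% among non-users and intra-couple correlation 0 or 0.3, while power for the total effect in the same data stays below 0.10.

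This part stands: a reader might infer that the 2% figure is impossible on every reading, and the documents do not support that. But the sentence speaks of the odds of reporting TRB, does not mention an indirect effect, and is separate from the later sentence on indirect pathways. As written, it fails.

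A second reply is that the drug-use figure is a slip for percentage points. That is plausible for the margin, but the article does not say so, and the contrast matters: with single cells at ICC 0.3 the slip would not restore .80. The intended meaning can only come from the simulation output.

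Third, the exact power depends on inputs the article omits. That is true of the second digit, but not of the conclusion, because the maxima cover all control rates and all ICCs from 0 to 1.

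**Conclusion.** The stated power is wrong as written for both outcomes: at most about 14% (margin) or 10% (single cell) for an odds ratio of 0.85, and about 5% for 0.98, against a stated figure above .80. This rests on two-sided alpha 0.05 and equal allocation. At control rates of 30-70%, the margin can detect an odds ratio of about 0.54-0.59 (ICC 0) or 0.49-0.55 (ICC 0.3).

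A reader might go further and infer that the trial is too small. The documents do not show that: the error lies in the stated effects, and the effect the simulations actually used is not visible. Nor do they support the opposite reassurance. The Background reports pilot SUM coefficients for drug use of −2.79 and −3.93 at 3 and 6 months (odds ratios exp(−2.79) = 0.06 and exp(−3.93) = 0.02), but only among men who viewed the CT videos. It reports no independent effect of the videos on drug use, and it gives no pilot effect size for TRB. These coefficients therefore cannot show that the size is adequate for CT alone or for TRB.

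The 1.0-point DAST statement is not in question here.

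**What to change.** Rewrite the detectable-effect sentences from the existing Mplus output. For each outcome give:
- the scale (odds ratio or percentage points);
- the contrast (marginal over the other component, or simple effect within one level of it);
- the effect type (total or indirect);
- the control rate, the ICC and alpha.

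Withdraw the 2% odds claim for TRB unless the output shows what was simulated and the sentence is relabelled accordingly. Do not substitute 15 percentage points, or an odds ratio near 0.55, without checking: at ICC 0.3 an odds ratio of 0.55 has power of only 0.68-0.80 even for 120 v 120 couples at control rates of 30-70%. Limit the statement that the effects are plausible from pilot data to the comparisons that the pilot covers, and do not extend it to CT alone or TRB.

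The cost is one paragraph and a re-reading of the output. Design, sample size and analysis need not change for this correction. The drawback is that the published detectable effects become less favourable.

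### The mediation power paragraph calls an association positive but prints it as −.45, and its printed inputs do not support power above .80 for every path, least of all the DAST chain

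*Protocol article*

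**What the plan says.** All the material is in one paragraph of the protocol article (Methods, Sample size).

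- Effects of CT: "improvements in self- disclosure communication (β = .13) and depression (β = −.16").
- Indirect effect on depression: "the indirect pathway between CT and depression through self-disclosure communication was of moderate size (β = −.12").
- Depression to outcomes: "Depression scores were, in turn, positively associated with the odds of drug use (β = −.45) and DAST scores (β = .06").
- Claim: the article takes these effects as preliminary estimates for Monte Carlo simulation and reports "power > .80 to detect the significance of direct pathways and implied indirect effects of intervention".

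On the simulation set-up, the section says: "These analyses therefore reflect a conservative analytic sample of 240 couples (480 individuals"). It also says "power was defined as the percentage of randomly generated samples in which the specified parameter was statistically significant", and "All simulated models were multi-level, nesting participants (at Level 1) within couples (at Level 2"). The article gives no alpha, within-couple correlation or standard deviations, and does not say whether the β values are standardised.

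**The concern.** Two things stand out.

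First, an association described as positive carries a minus sign, while the DAST coefficient in the same sentence is positive. These numbers are said to have fed a simulation, so a reader cannot tell which direction was simulated. The sign decides whether the proposed mechanism has CT lowering or raising drug use.

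Second, a path of .06 is very small for a sample of 480 if it is a standardised coefficient, yet the power sentence makes no exception for it. If the claim is too generous, a null mediation result for DAST could be read as well powered when it was not.

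A third figure deserves a check. The indirect effect of −.12 with a first path of .13 implies a very large second path from self-disclosure to depression.

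**Working it through.** **Inputs from the Sample size section.** 240 couples, 480 individuals; CT to self-disclosure .13; CT to depression −.16; CT to depression through self-disclosure −.12; depression to drug use −.45 (called positive); depression to DAST .06; claimed power above .80.

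**Assumptions, not in the article.** Two-sided alpha .05; equal allocation (120 couples with CT, 120 without); within-couple correlation (ICC) 0, .3 or .5; standardised coefficients, except in step 6.

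**1. The plan's own figure.** The claim of > .80 cannot be reproduced definitively, because alpha, ICC, coefficient scale and SDs are not given. The steps below test which paths reach it under the stated assumptions.

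**2. Sign.** CT to depression to drug use:
- as printed: (−.16)(−.45) = +.072
- following the word positive: (−.16)(+.45) = −.072

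Two-sided power depends on |.45| and does not change.

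**3. Power of single paths.** Power = Φ(|β| / √((1 − β²)/n) − 1.96). For couple-level CT paths n = 480/(1 + ICC), that is 480, 369 and 320. For depression to outcome n = 480.

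| Path | ICC 0 | ICC .3 | ICC .5 |
|---|---|---|---|
| CT to depression, .16 | .94 | .88 | .83 |
| CT to self-disclosure, .13 | .82 | .71 | .65 |

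- The .13 path reaches .80 only if ICC is at most about .05.
- Depression to DAST, .06: .06 × √480 / √(1 − .0036) = 1.317; 1.317 − 1.960 = −.643; power .26 (one-sided: .37).
- Individuals needed for 80%: (1.960 + .842)² × (1 − .0036)/.0036 ≈ 2,172.
- Smallest standardised β with 80% power at n = 480: about .127.
- Depression to drug use, |.45|: about 1.00 if standardised. Read as a logit per SD of depression, about .98 to above .99 for drug-use prevalence of .3 to .8.

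**4. Indirect effects.** Two-level simulation, 5,000 replications, 240 couples:

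| Chain | Test | ICC 0 | ICC .3 | ICC .5 |
|---|---|---|---|---|
| CT, depression, DAST | joint significance | .24 | .22 | .20 |
| CT, depression, DAST | Sobel | .12 | .10 | .08 |
| CT, depression, drug use (|.45|) | joint significance | .94 | .87 | .83 |

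As a check on the first row, the product of the single-path powers at ICC 0 is .944 × .260 = .245.

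**5. Implied second path.** −.12/.13 = −.92 (−.85 to −1.00 allowing for rounding). If standardised, self-disclosure would account for about .92² = 85% of the variance in depression. The three figures still cohere: −.16 − (−.12) = −.04 is left as the direct effect.

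**6. Could an unstandardised scale rescue .06?**
- It reaches .127 in standardised terms once SD(depression)/SD(DAST) is about .127/.06 ≈ 2.1.
- If the same raw scale applies to CT to depression (0/1 coding, 240 v 240 individuals, independence), 80% power for −.16 needs SD(depression) ≤ .16/(2.80 × √(2/240)) ≈ .63.
- Together these force SD(DAST) ≤ .63/2.1 ≈ .30. The 1.0-point DAST reduction in the same section would then exceed 3 SD.
- With SD(DAST) = 1 and SD(depression) = 2.1, the CT-to-depression path has power of about .13.
- The other route is for covariates to explain about 78% of DAST variance: 1 − (.06 × √480/2.80)² ≈ .78.

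**The case against.** The strongest reply is that the article never calls these coefficients standardised. One of them concerns the odds of drug use and may be a logit coefficient, and DAST effects elsewhere in the section are in raw points. A raw .06 can have ample power if depression has a much wider spread than DAST. This stands as far as it goes: a reader might infer that > .80 cannot be right, and the article does not prove that. But β is used here where the pilot results in the Background use B, and the effects are labelled small and moderate, which points to standardised values. A uniform raw scale rescues .06 only with the implausible SDs of step 6. What remains is mixed scales within one chain or strong unstated covariates.

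Other stronger readings also fail:

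- **That −.92 is a contradiction.** It is implausible if standardised, but the figures cohere and it may be unremarkable on a raw scale. The remark that effects are generally small is about viewing the videos, not about the link from self-disclosure to depression.
- **That the sign error lowers power.** It does not.
- **That power should be computed with n = 240.** That treats partners as perfectly correlated, which nothing in the article supports.
- **That the design is underpowered overall.** The main-effect power statements do not rest on these coefficients.

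It is also fair that the mental-health and communication mediators are exploratory under Moderation/mediation analyses, and that the statement in Objectives about powering for indirect effects concerns transmission risk behaviour through drug use. Alpha, ICC and SDs may properly sit in the full protocol; their absence is not the point here.

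**Conclusion.** The conflict between word and sign is certain on any scale and must be reconciled. It reverses the implied direction of the CT effect on drug use through depression (+.072 against −.072) and leaves two-sided power unchanged.

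The blanket power claim is not supported by the printed inputs. On the standardised reading with two-sided alpha .05, it fails clearly for depression to DAST (about .26) and for the indirect effect through it (about .20 to .24 by joint significance). It is doubtful for CT to self-disclosure unless the within-couple correlation is near zero. It holds for CT to depression and, taking |.45|, for the drug-use chain. The −.92 is a figure to check, not a demonstrated error.

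The consequence is confined to how mediation results, mainly for DAST, would be interpreted. The 240-couple analytic sample and the main-effect power are untouched.

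**What to change.** 1. Check the pilot output and correct either the sign of .45 or the word describing the association.
2. In the same check, confirm .13, −.12 and −.16, since together they imply −.92.
3. State whether each coefficient is standardised, raw or a logit.
4. Re-run the Monte Carlo simulation with the confirmed values and report power path by path, for direct and indirect effects.
5. Restrict the > .80 statement to the paths that reach it, and drop it for the DAST chain unless the re-run supports it.

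The cost is a re-run of existing simulations and a few edited sentences. No change to design or sample size follows. The downside is that some stated mediation power will probably fall.
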